We propose a novel integration of two exemplar, AAP-recommended EBPIs delivered at pediatric well visits:

**1) HealthySteps (HS)** utilizes a stepped-care approach including universal screening for ACEs and child developmental delays. Families with increased concerns also receive customized support and referral for additional services. HS is rapidly becoming standard of care in pediatrics with implementation in 25 states and over 200 sites. Whereas HS has impacts on family vulnerabilities (e.g., maternal depressive symptoms^13,14^), it has limited impacts on PCEs, which are not addressed through direct HS services. Thus, even as screening and services to address ACEs have become standard of care in pediatrics, ***this suggests the need for additional strategies to target ERH and child outcomes in order to improve effectiveness*.**

**2) PlayReadVIP** has the potential to address this gap through a focus on PCEs by video-recording the parent and child playing with a toy or reading a book with immediate, real-time review and feedback to identify and reinforce strengths in the interaction. PlayReadVIP has beneficial impacts on parenting assets (e.g., learning materials^15^), ERH/cognitive stimulation (e.g., reading aloud^16^), and child outcomes.^17^ PlayReadVIP’s low cost and strong evidence base have resulted in increased implementation in pediatrics, with 13 sites in 3 cities.

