The overarching objective of this protocol, then, is to understand both the effectiveness and practical implementation of the HS+PlayReadVIP model in real-world pediatric primary care environments. Currently, implementing early childhood interventions like HS+PlayReadVIP in pediatric primary care presents several challenges; such as time limitations, limited funding, staffing Issues, lack of training , not reaching the diverse patient polulation and not addressing social determinants directly. This protocol focuses on 2 principle aims that will asses the impact of the integrated HS+PlayReadVIP model on various outcomes : Aim 1: Assess the effectiveness of the HS+VIP model on parent-child relational health, parent mental health, and parenting behaviors compared to standard HealthySteps (HS). And Aim 2: Evaluate the implementation outcomes of the HS+VIP model, including feasibility, acceptability, appropriateness, reach, engagement, and fidelity. Working on these challenges is crucial for the successful implementation and sustainability of early childhood interventions in pediatric primary care settings.

The overall goals are :

1. Aim 1: Determine whether the integrated HealthySteps (HS) and Video Interaction Project (VIP) model has greater impacts on parenting and early child development (ECD) compared to standard HS alone.
2. Aim 2: Understand how and why the integrated HS+VIP model works by examining the mechanisms driving its impacts and the contexts influencing its implementation.

Together, Aim 1 and Aim 2 will:

- Demonstrate the value of integrating evidence-based preventive interventions in pediatric primary care to address disparities in child development.
- Generate actionable knowledge about how to implement and sustain such integrated models effectively in diverse healthcare settings.

By addressing these aims, the study seeks to provide comprehensive insights into both the effectiveness and practical implementation of the HS+VIP model in real-world pediatric primary care environments.

This project will be led by [name], a developmental psychologist with a primary appointment as compensated faculty in the Department of Pediatrics at NYU Grossman School of Medicine.

Primary endpoints: Parenting practices, parent-child relationships and child development.

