## Primary Objective

There are two primary objectives of this study:

**Aim 1. Implement the optimized integrated HS+VIP model (formalized in Aim 1), and conduct an effectiveness-implementation study (Hybrid I design).**

1. Examine effectiveness of the integrated HS+VIP model, including parent mental health, parenting behavior, and early child development outcomes.
2. Examine implementation outcomes, including reach, appropriateness, acceptability, feasibility, and fidelity, using an integrated RE-AIM^18^ and CFIR^19^ framework.

**Aim 2. Examine health disparities mechanisms underlying effectiveness-implementation outcomes.** Using a mixed methods design, we will examine whether HS+VIP impacts are 1) mediated by impacts on parent assets/vulnerabilities and ERH or 2) moderated by CFIR contextual factors or RE-AIM domains.

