## Study Endpoints

### Primary Study Endpoints

Parent mental health, parenting practices, parent-child interaction, parent-child relationship, social determinants of health, child development, intervention feasibility, acceptability, reach, and participant engagement. These outcomes will be measured through surveys, interviews, parent-child observations, and direct assessments of child development (see Section 6 for additional details on specific measures).

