# Behavioral/Social Intervention

## Study Behavioral or Social Intervention(s) Description

The study integrates two evidence-based programs, HealthySteps (HS) and PlayReadVIP, into a combined intervention (HS+PlayReadVIP) to support families and improve early child development (ECD).

HealthySteps (HS):

1) Focuses on addressing Adverse Childhood Experiences (ACEs) and family stressors.

2) Provides parenting guidance, mental health support, and care coordination.

3) Delivered during well-child visits by an HS specialist.

Video Interaction Project (VIP):

1) Promotes Positive Childhood Experiences (PCEs) and strengthens parent-child interactions.

2) Involves recording and reviewing videos of parents engaging with their child to provide feedback and encourage positive practices.

3) Families receive toys, books, and guides to extend activities at home.

Integrated HS+VIP Model:

1) Combines HS and VIP to address both ACEs and PCEs.

2) Delivered during the same pediatric visits for high-risk families, saving time and enhancing impact.

3) Designed to be culturally sensitive and family-centered.

Setting and Delivery:

- Conducted at the NYU Langone Sunset Park Family Health Center, targeting low-income, minority families.
- Delivered over 24 months during routine pediatric visits.

Goals:

- Improve parenting practices and Early Relational Health (ERH).
- Enhance cognitive, language, and social-emotional development in children.
- Reduce ECD disparities by addressing both risks and opportunities within families.

This integrated approach leverages the accessibility of pediatric primary care to maximize its reach and effectiveness.

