# Statistical Considerations

## Statistical and Analytical Plans

***Effectiveness Outcomes***

Initial ANOVA and Chi-square tests will be conducted to examine baseline equivalence of randomly assigned groups. Analyses with sex as a biological variable, including moderation and subgroup analyses, will be performed. Covariate entry (e.g., sociodemographics) will be decided based on model fit criteria, and sensitivity analyses will be performed for post-randomization risks.

Missing data and attrition: The research team has expertise in minimizing missing data. In addition, multiple imputation (MI)^160^ will be used to replace item-level data using the rich array of concurrently collected variables and prior responses. If an entire measure/survey is missing, we will use chained equations with lagged (in time) variables^161^ using all available information to build a large set of imputed datasets. Estimates will be combined using Rubin’s rules.^160^ When data are Missing at Random, likelihood-based methods provide unbiased estimates of population parameters even when panels are incomplete. In addition, we will use attrition analyses^162^ to examine whether attrition is related to baseline characteristics.

Tests of hypotheses: In order to examine the added value of HS+VIP in comparison to the standard HS model, we will focus on outcomes related to ERH and ECD where we expect the effects of standard HS to be substantially smaller than the integrated HS+VIP model. Impact analyses at each assessment timepoint will be conducted using ordinary least squares (OLS) regression in an intent-to-treat (ITT) framework, adjusted for baseline sociodemographic covariates. In addition, structural equation models (SEM)^163^ will be used to examine family outcomes over time. This will allow us to examine whether initial levels and trajectories in parent well-being, parent-child interaction, and ECD vary between participants, and whether that variation is explained by assignment to HS+VIP or standard HS.

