## Statistical Hypotheses

***Effectiveness***

*Null Hypothesis (H0):* The integrated HS+PlayReadVIP intervention does not significantly improve parenting practices and relational health outcomes compared to HS alone.

*Alternative Hypothesis (H1)*: The integrated HS+PlayReadVIP intervention significantly improves parenting practices and relational health outcomes compared to HS alone.

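### Parent mental health is a listed primary endpoint, yet it lies outside both the stated focus of the hypothesis tests and the formal effectiveness hypothesis

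*Protocol*

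**What the plan says.** The protocol gives differing accounts of which outcomes carry the effectiveness conclusion.

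- **Aim 1.** Section 3.1 reads: "Examine effectiveness of the integrated HS+VIP model, including parent mental health, parenting behavior, and early child development outcomes". Section 2.1 also includes parent mental health in its first statement of Aim 1, in second place.
- **Primary endpoints.** Section 4.2.1 begins: "Parent mental health, parenting practices, parent-child interaction, parent-child relationship, social determinants of health, child development". The Endpoints row of the Protocol Summary and the primary-endpoint line that closes section 2.1 both leave parent mental health out.
- **Tests of hypotheses (section 9.1).** To examine added value over standard HealthySteps (HS), "we will focus on outcomes related to ERH and ECD where we expect the effects of standard HS to be substantially smaller" than those of the integrated model. ERH is early relational health and ECD is early child development. The next sentence is: "Impact analyses at each assessment timepoint will be conducted using ordinary least squares (OLS) regression in an intent-to-treat (ITT) framework", with adjustment for baseline sociodemographic covariates. It has no outcome list of its own.
- **Formal hypothesis (section 9.2).** The alternative is: "The integrated HS+PlayReadVIP intervention significantly improves parenting practices and relational health outcomes compared to HS alone".
- **Measurement (section 7.1.1).** The Edinburgh Depression Scale and the Perceived Stress Scale appear under effectiveness outcomes, at baseline, 12 and 24 months.

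**The concern.** The trial asks what PlayReadVIP adds to standard HS. Section 9.1 explains its focus by where the comparator is expected to do little. Section 2.1 says where the comparator does work: "Whereas HS has impacts on family vulnerabilities", with maternal depressive symptoms as the example. The listed primary endpoint on which standard HS is strongest is therefore the one left out of the focus and the hypothesis.

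The protocol itself allows that integration may not be purely additive. Section 9.5 cites possible non-additive impacts as a reason for a conservative effect size. Section 9.1 scores HS and VIP fidelity separately to see whether joint delivery brings its own difficulties.

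At stake is the completeness of the answer to Aim 1. The trial could meet its stated alternative on parenting and relational health and report success, with no committed 24-month estimate of whether parents' depression or stress was better, the same or worse than under standard HS.

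**Working it through.** **Step 1. Where each section places parent mental health.**

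| Protocol section | Parent mental health |
| --- | --- |
| Summary, Endpoints row | absent |
| 2.1, first statement of Aim 1 | included |
| 2.1, primary-endpoint line | absent |
| 3.1, Aim 1 | included, named first |
| 4.2.1, primary endpoints | included, named first |
| 7.1.1, effectiveness measures | included, three time points |
| 9.1, focus of tests | outside ERH/ECD |
| 9.1, regression (OLS) sentence | neither named nor excluded |
| 9.1, SEM | parent well-being, by assigned arm |
| 9.1, mediation | 12-month screen of parent mediators |
| 9.2, H0/H1 | absent |

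**Step 2. What the two analyses that reach it deliver.** The SEM asks whether trajectories in parent well-being are explained by assignment. That is a between-arm comparison, but the measures table has no construct of that name, so the link to the Edinburgh and Perceived Stress scales is not stated. The mediation plan tests only mediators on which the new model has a significant impact at 12 months, which implies an arm comparison on parent vulnerabilities at that visit. It serves to select mediators and stops at 12 months. Neither analysis enters the section 9.2 hypothesis.

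**Step 3. Reproduce the plan's power figure.** Inputs from section 9.5: 500 enrolled, 15-20% attrition, d = .30, alpha = .05. Two-sided testing and 200 per arm at analysis are assumed. Randomization limits the arm difference to 4 at enrollment, so near-equal arms are plausible.

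- Final sample: 500 × (1 − 0.20) = 400, or 425 at 15% attrition.
- Power at d = .30 with 200 per arm: Φ(0.30 × √(400/4) − 1.96) = Φ(1.04) = 85.1%; the noncentral t gives 84.9%. This agrees with the stated figure of more than 80%.

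**Step 4. What the same sample gives for a mental-health score.** The correlation r between baseline and follow-up score is an assumption; the protocol gives none.

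- CI half-width = 1.96 × √(4/400) × √(1 − r²).
- Power for a 0.2 SD loss = Φ(0.2 × √(400/4) / √(1 − r²) − 1.96).

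| r | Half-width (SD) | Power for a 0.2 SD loss |
| --- | --- | --- |
| 0 (unadjusted) | 0.196 | Φ(0.04) = 52% |
| .4 | 0.180 | Φ(0.22) = 59% |
| .5 | 0.170 | Φ(0.35) = 64% |
| .6 | 0.157 | Φ(0.54) = 71% |

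Unadjusted, the smallest difference detectable with 80% power is 0.28 SD. A loss as large as the planned gain (0.30 SD) has 85% power.

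**The case against.** A reader might infer that parent mental health gets no impact test at all. The protocol does not support that. Section 9.1 speaks of a focus and excludes nothing, and its SEM relates parent well-being to assigned arm. The mediator screen needs a 12-month arm comparison. Section 9.4 refers the primary-endpoint methods back to section 9.1, and section 9.4.4 repeats the analyses at 12 months across parent and child characteristics. An outcome-by-model list may also sit in a statistical analysis plan, which is not shown. All of this stands and limits the point.

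A reader might also infer that outcomes were chosen to favor the new arm. Section 9.2 omits child development too, where section 9.1 expects the new arm to do better, so loose drafting is the likelier explanation. A declared focus on what the added component targets is ordinary practice.

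Nor does the protocol say that video coaching displaces HS support. Section 6.1 describes joint delivery thus: "Delivered during the same pediatric visits for high-risk families, saving time and enhancing impact". A cost to parents' mental health is a possibility to be estimated; nothing in the protocol predicts it.

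These replies do not remove the mismatch. It lies between statements the protocol itself makes: one section makes the outcome primary, and the hypothesis section omits it.

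**Conclusion.** The concern holds as an inconsistency with a practical consequence. Parent mental health is a listed primary endpoint and an Aim 1 outcome, but it is outside the test focus and outside H0/H1, and two of the endpoint lists omit it. Under section 9.2 as worded, a worse result on it leaves the effectiveness conclusion untouched.

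The planned data can give a usable estimate, with a half-width of 0.16 to 0.20 SD depending on baseline adjustment. It would be wrong to infer from this that a 0.2 SD worsening would show up dependably, since power is only about 52% to 71% over the range examined. The case is therefore for reporting an interval, not for relying on a significance test. The figures rest on 400 analyzed families in equal arms, two-sided alpha of .05 and assumed baseline correlations of up to .6.

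**What to change.** 1. Reconcile the Protocol Summary and sections 2.1, 3.1, 4.2.1, 9.1 and 9.2 on whether parent mental health is a primary endpoint. If it is not, remove it from section 4.2.1 and say why.
2. In section 9.1, name the Edinburgh Depression Scale and the Perceived Stress Scale at 12 and 24 months in the intent-to-treat OLS models. Adjust each for its own baseline score, since the section now names only sociodemographic covariates. Report two-sided 95% confidence intervals beside the ERH and ECD results, whatever their direction.
3. If it stays primary, add a two-sided parent mental health hypothesis to section 9.2 and handle it under the false discovery rate approach of sections 9.4.4 and 9.4.6.

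The cost is wording and four regressions (two scales at two visits) on data already scheduled. Step 3 makes the test family slightly larger, with a small loss of power for the other outcomes.

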# Schematic of Study Design

Approximately 1000 **individuals** -500 parent-infant dyad

dyad)

Randomize

Parent surveys, demographic information, and baseline measures of parenting assets, vulnerabilities

Families receive intervention (HS+PlayReadVIP or standard HS)

Parenting, ERH, and ECD outcomes, as well as intervention acceptability assessed through surveys, observations, and direct assessments

Parenting, ERH, and ECD outcomes, as well as intervention acceptability assessed through surveys, observations, and direct assessments

Qualitative interviews focusing on family needs, resources, and context

Baseline

0–24 months

Child age 12m; 6+ months post-enrollment

Child age 24m; 18 months post-enrollment

End of study (child age 24m)

Families with infants ≤6M, randomized into HS+PlayReadVIP or standard HS groups

Approximately **25** individual care providers

Acceptability & appropriateness of intervention; clinic climate & processes

Qualitative interviews of implementation outcomes

Acceptability & appropriateness of intervention; clinic climate & processes

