## Inclusion Criteria for parent-child dyads

In order to be eligible to participate in this study as a parent/child dyad, including one parent and one child, the dyad must meet all of the following criteria:

1. Parent is a biological parent or legal guardian and at least 18 years of age
2. Infants must be ≤6 months old at the time of enrollment.
3. Parents/guardians must speak either English or Spanish to ensure they can fully engage with the intervention and assessments.
4. Families must be identified as Tier 3 HealthySteps participants, indicating higher levels of need based on clinic screening for factors such as:Adverse Childhood Experiences (ACEs) and parenting challenges or vulnerabilities.
5. Parent is able to willing to provide consent for their own and their child’s participation.

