## Duration of Study Participation

Duration of study participation (screening, enrollment, randomization, intervention delivery, and follow-up) for parent-child dyads is approximately 2 years – from infant birth through age 2 follow up, which may take place prior to the child’s 3^RD^ birthday. Participation for care providers is approximately 1 year, with surveys and qualitative interviews taking place to coincide with age 12m and 24m parent-child assessments.

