# Study Procedures and Schedule

## Study Procedures/Evaluations

**Overall Study Procedures:**

For all parent/child dyads who are enrolled in the RCT, we will administer assessments at baseline, 12 months, and 2 years to measure outcomes (e.g., parenting assets/vulnerabilities, parenting practices/parent-child relationship, child development) and covariates (e.g., socio-demographics, biological risk) for Specific Aims 1 and 2. Assessments will include a combination of parent survey, observation of parent/child, direct assessment of child, and medical record review. In addition, we will conduct two assessments with care providers within the clinic to assess intervention implementation. All assessments will be completed by highly trained research assistants blind to group/intervention status.

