### Intermediate Visits

**Visit 2 (Day 180 +/- 90)**

- Record adverse events as reported by participant or observed by investigator.
- Administer questionnaires/surveys of parent well-being, parenting, and child development, and conduct parent-child observations
- Administer questionnaires to parents and care providers regarding program acceptability, appropriateness, and reach.
- Record participant’s engagement to intervention program and program fidelity and reach.

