### Final Study Visit

***Final Study Visit (Visit 3, Day 540 +/- 90)***

- Record adverse events as reported by participant or observed by investigator.
- Administer questionnaires/surveys of parent well-being, parenting, and child development, and conduct parent-child observations
- Administer questionnaires to parents and care providers regarding program acceptability, appropriateness, and reach.
- Record participant’s engagement to intervention program and program fidelity and reach.
- Conduct qualitative interviews regarding program implementation with parents and care providers.

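### The rules that time the 12M and 24M visits disagree, so allowed child ages span about a year or more, and the impact model does not commit to adjusting age-dependent child outcomes for age at assessment

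*Protocol*

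**What the plan says.** **Visit timing.**
- Inclusion Criteria: "Infants must be ≤6 months old at the time of enrollment".
- Schematic of Study Design: the last assessment is labelled "Child age 24m; 18 months post-enrollment".
- Final Study Visit: "Final Study Visit (Visit 3, Day 540 +/- 90" days, counted from the enrollment visit as Day 0.
- Duration of Study Participation: an "age 2 follow up, which may take place prior to the child"'s third birthday.
- Intermediate Visits: the 12M assessment is "Visit 2 (Day 180 +/- 90" days on the same clock.

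**Analysis.** Under Effectiveness Outcomes, the impact analyses are intent-to-treat OLS regressions at each timepoint, "adjusted for baseline sociodemographic covariates". The same section adds: "Covariate entry (e.g., sociodemographics) will be decided based on model fit criteria". The description of study procedures gives examples of what is collected: "covariates (e.g., socio-demographics, biological risk", and so on. Child age at assessment is not named as a covariate anywhere in the protocol.

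**Outcomes and power.** Child outcomes include communication inventories at 12M and 24M and directly administered expressive and receptive vocabulary tests at 24M. The protocol does not say whether raw or age-normed scores are analysed. The Sample Size section claims more than 80% power for d of about .3 with 400 families analysed and alpha = .05.

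**The concern.** Vocabulary and communication develop quickly in the second year of life. If the visit called 24M can take place at very different ages, part of the variation in a raw score is only the child's age on the day of testing. An analysis that ignores age counts this as residual noise. If one arm were seen later on average, its children would also be older and could score higher for that reason.

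The meaning of the endpoint is also at stake. A 24M result should refer to a definable age, and the timing rules do not define one. Covariate entry by model fit does not settle the matter, because it lets age enter for some outcomes and not for others after the data are seen.

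**Working it through.** **1. Reproduce the stated power.** Inputs from the Sample Size section: 400 analysed (200 per arm assumed), d = .30, alpha = .05 (two-sided assumed).
Power = Φ(d × √(n/2) − 1.96) = Φ(.30 × 10 − 1.96) = Φ(1.04) = .851. The noncentral t gives .849. The claim of more than 80% is confirmed.

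**2. Ages allowed at each visit** (30.44 days per month; enrollment at 0 to 6 months).

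| Visit | Youngest | Oldest | Span |
|---|---|---|---|
| 12M, Day 180 +/- 90 | 90/30.44 = 3.0 months | 6 + 270/30.44 = 14.9 months | 11.9 months |
| 24M, Day 540 +/- 90 | 450/30.44 = 14.8 months | 6 + 630/30.44 = 26.7 months | 11.9 months |

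Day 540 itself is 17.7 months after enrollment, so a visit exactly on target occurs at 17.7 to 23.7 months of age. The schematic's equation of age 24 months with 18 months post-enrollment holds only for a child enrolled at 6 months. If the third-birthday allowance is added to the day window, ages run from 14.8 to just under 36 months, about 21 months. These results need no assumption beyond the protocol's own figures.

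**3. Effect on power if age is ignored.** Three assumptions are not in the protocol: raw scores are analysed; d = .30 is defined among children of the same age; scores grow by g = .10 to .20 within-age SD per month. Enrollment age and visit timing are taken as uniform.
- Age SD under the day window: √(36/12 + 36/12) = 2.45 months, rounding the 180-day window to 6 months.
- Age SD with +/- 90 days around a fixed age: √(36/12) = 1.73 months.
- Variance inflation: V = 1 + (g × SD)². Unadjusted effect: .30/√V.

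| Timing rule | g | V | Unadjusted d | Power |
|---|---|---|---|---|
| Day window | .10 | 1.06 | .291 | .830 |
| Day window | .20 | 1.24 | .269 | .769 |
| +/- 90 days around a fixed age | .10 | 1.03 | .296 | .840 |
| +/- 90 days around a fixed age | .20 | 1.12 | .283 | .809 |

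The noncentral t gives values lower by .001 to .002.

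**4. The other definition of d.** If d = .30 is on the total SD, age variation included, unadjusted power stays at .851. Adjusting for age then raises the effective d to .30 × √V. Under the day window this is .309 to .334, with power Φ(1.13) = .87 to Φ(1.38) = .92. Omission then forgoes precision but does not breach the stated power.

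**5. Bias.** The shift in the contrast is g × (difference in mean age between arms). An illustrative half-month difference gives .5 × .10 = .05 to .5 × .20 = .10 SD, against a target of .30. Chance alone gives a standard error for that difference of 2.43 × √(2/200) = 0.24 months, taking the window as exactly 180 days.

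**The case against.** **The covariate list is not closed.** A reader might infer that the model adjusts for sociodemographics only and so excludes age. The protocol does not say that. Its covariate examples are open-ended, entry is decided by model fit, and a statistical analysis plan that is not shown could name age. This stands: age is uncommitted, not excluded. What remains is that a fit-based rule, as stated, does not guarantee age for the outcomes that need it.

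**The power loss is conditional.** It disappears with age-normed scores or with d on the total SD. With +/- 90 days around a fixed age, power stays above 80% under both growth assumptions. The protocol also lists temperament, social-emotional and behaviour questionnaires, for which no age slope is given. All of this stands, so a loss for every child outcome is not supported. A steeper fall, to .81-.69, can be obtained by assuming an age SD of 3.5 months for a tail to the third birthday. The protocol gives no such distribution, and that figure should not be relied on.

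**Bias is not shown.** A reader might infer that late visits will skew the comparison. Randomisation balances enrollment age in expectation, assessors are masked, both programs are delivered at well-child visits, and the retention procedures are not described as differing by arm. Participants and interventionists are unmasked, so unequal visit timing is possible, but nothing in the protocol shows it.

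**Age at assessment is partly post-randomisation.** This is correct, and the fix has to allow for it.

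**Conclusion.** The concern holds in a limited form. The contradiction in timing is firm and rests only on the protocol's own figures: three statements about the last visit cannot all define the same assessment, and the day windows alone permit an 11.9-month range of ages at both 12M and 24M.

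The analysis point is a worthwhile improvement, not a demonstrated error. Its size rests on raw scores, d at fixed age and the assumed growth range. On those terms power falls by about .02 to .08 under the day window and by about .01 to .04 with +/- 90 days around a fixed age. Only the upper growth rate combined with the day window takes it below 80%. The documents do not support the stronger conclusions that age is excluded from the model, that all child outcomes lose power, or that the contrast is biased.

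**What to change.** 1. Reconcile the schematic, Duration of Study Participation, Intermediate Visits and Final Study Visit so that the 12M and 24M assessments are each defined on one scale with one window. Which timing is intended is for the study team to decide.
2. For the age-dependent child outcomes (vocabulary and communication in particular), pre-specify exact child age at assessment as a covariate, or age-standardised scores where they exist, instead of leaving age to model fit.
3. Include age at assessment in the imputation model.
4. Report age at assessment by arm at both timepoints.
5. Because visit timing is partly post-randomisation, add a sensitivity analysis that adjusts for age at enrollment only.

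The cost is a change of wording. Birth and visit dates supply the variable, so no new data collection is needed. The one statistical drawback, adjusting for something that could be affected by arm, is addressed by items 4 and 5.
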